##### Attitudes Toward Inclusive Education

The parents’ attitudes toward inclusive education was measured using the Attitudes Toward Inclusion/Mainstream scale [43]. This questionnaire, consisting of 18 items that are rated on a 5-point Likert scale (1=strongly agree to 5=strongly disagree), assesses the overall attitude of parents toward the inclusion of students with disabilities in mainstream schools, including 4 dimensions (benefits factor, satisfaction with special education, teacher ability and inclusion support, child rights). The Multidimensional Attitudes Towards Inclusive Education Scale [44] was selected to evaluate teachers’ attitudes toward the inclusion of students with disabilities in mainstream schools. It consists of 18 items assessed using a 6-point Likert scale (1=strongly disagree to 6=strongly agree) and measuring 3 dimensions (cognitive, affective, behavioral).

#### Secondary Outcomes

##### Perception of Caregiver Burden

Parents and professionals completed the Zarit Burden Inventory Short Form [45,46], which consists of 12 items assessing the individual perception of their burden. Each item is scored between 1 point and 5 points (1=never to 5=almost always), and the total score is the sum of all item scores. The higher the score is, the higher the burden is, with the following cut-offs: no to mild burden (0-10), mild to moderate burden (10-20), and high burden (>20). For parents, the assessment was completed with the Caregiver Strain Questionnaire [47] to evaluate the familial burden through 21 items using a 5-point Likert scale (1=not at all to 5=very much) and 3 dimensions (objective burden, internalized subjective burden, and externalized subjective burden). The Caregiver Strain Questionnaire has been specifically validated with families of children with disabilities, including NDD or ASD. For professionals, the level of burnout was assessed using the French version of the Maslach Burnout Inventory [48], a 22-item scale using a 7-point Likert scale (1=never to 7=every day) that evaluates emotional exhaustion, depersonalization in relationships with others, and a sense of reduced personal accomplishment in one’s work.

##### Stakeholders’ Quality of Life

Parents and professionals completed the WHOQOL-BREF [49], a 26-item scale using a 5-point Likert scale (1=Very Low, Very Dissatisfied, Not at all, Very Difficult, Never to 5=Very High, Very Satisfied, Extremely, Very Easily, All the Time) recommended by the World Health Organization to assess individuals’ quality of life based on 4 dimensions (physical health, psychological health, social relationships, environment). The quality of life of the family was assessed using the Beach Center Family Quality of Life scale [50], adapted into French by Rivard et al [51]. This scale, consisting of 25 items using a 5-point Likert scale (1=Slightly Important, Very Dissatisfied to 5=Very Important, Very Satisfied), measures 5 dimensions of family quality of life: family interactions, parenting, emotional well-being, physical and material well-being, and disability-related support.

##### Child’s Quality of Life

The pupil’s quality of life was assessed using the Pediatric Quality of Life Inventory [52]. The Pediatric Quality of Life Inventory is composed of 23 items using a 5-point Likert scale (0=never to 4=almost always) assessing children’s physical, emotional, social, and school functioning through self-report (completed by children) and proxy report (completed by parents).

##### Child’s Perception of School Life

The student's sense of school inclusion was evaluated using the single-item inclusion scale by Aron et al [53], which measures 7 levels of the sense of inclusion and has been adapted to assess the sense of inclusion in both the school and peer group contexts. School satisfaction was evaluated using an 8-item subscale that uses a 7-point Likert scale (1=strongly disagree to 7=strongly agree) derived from the French adaptation of the Multidimensional Students’ Life Satisfaction Scale [54,55].

##### Measurement of Technology Experience (Experimental Group Only)

To assess the potential effect of prior technology skills on the use of CoEd, parents and professionals completed the Computer Usage Questionnaire [56] that consists of a self-reported measure of 18 questions asking for the frequency (5-point scale ranging from never to very often) of different computer activities and software usage.

To address the specific user experience with the CoEd application, the User Experience Questionnaire short form [57] was selected as the measurement. It uses a 7-point Likert scale (–3=fully agree with negative term to +3=fully agree with positive term) of subjective perceptions of users in terms of both the hedonic and pragmatic dimensions toward a given product and according to a benchmark for digital products. The Technology-based Experience of Need Satisfaction-Interface [58] is related to the self-determination theory framework for assessment and uses a 5-point Likert scale (1=Do Not Agree to 5=Strongly Agree) to assess basic psychological need (autonomy, competence, relatedness) satisfaction through the interaction with the interface or system. Satisfaction of these needs is arguably associated with sustained engagement with a technology.

Complementary to the subjective measures, direct measures of CoEd use and usage are collected through active interactions (log data) with this web application, in particular the number of times the app was opened and the number of exchanged posts (Table 1).

### Presentation of the CoEd Technology

Specific to the French school context, the CoEd application (Figure 2) is accessible through a web browser and allows users to view and edit one or multiple student files. Users need to be registered by the administrator and can log in with an email and password. Roles—parent, teacher, or external professional—are assigned during registration, offering equal file access rights. A designated moderator role, open to any team member by consensus, is suggested for content moderation.

**Figure 2 figure2:**
[figure not shown]
Screenshots of different tabs from the CoEd app.

Once logged in, the user can access the student's file, which consists of 6 tabs: profile, skills, meetings, compendium of tips, news, contacts.

As an identity card, the profile provides key main information to know about the child. A “What’s up?” block allows users to be informed of new content in the folder.

The skills section allows users to review the child’s skill assessment. Two skill referentials are provided: (1) a formal IEP evaluation (ie, Geva-Sco scale for French IEP) and (2) a custom skill referential, where users can determine the categories and skills they wish to assess according to the child’s profile.

The meetings tab allows user awareness of past and upcoming meetings about the child. This section also provides an interface to automatically generate reports about past meetings in PDF format, which are accessible by all users.

On the compendium of tips tab, users can share tips, aids, and adjustments that they successfully used with the child in particular situations. They can receive feedback from the other team members.

The news section is dedicated to punctual and rapid information sharing, such as daily events or feedback and particular events.

On the contacts tab, all team members related to the child’s folder are identified, including their role in the team and contact information.

### Procedure

When the participants were assigned to the CoEd intervention condition, the researchers created the child’s page and the users’ logins on the CoEd application. The participants may provide initial general information to be put on the child’s page by the researchers. At the beginning of the study and after collecting baseline measures, the participants of the CoEd intervention condition received a user manual and video tutorials to help them handle the application, and additional training could be provided by the researchers if needed. Once the study began, the participants were asked to use the application at least once a week but were free to use it as often as they wanted.

The participants from the control group did not receive any intervention and were asked to function as usual.

All questionnaires were administered through online forms. Every participant received an identification number, which was used to anonymize the data collected. At the date of measurement (baseline, 3-month follow-up, 6-month follow-up), participants were instructed by mail to complete the questionnaires. The data collection was monitored by the researchers, and the participants who did not answer were reminded once a week by mail or phone. If participants remained unreachable for more than 6 weeks, they were labeled as “lost” and excluded from the trial.

The data collected through forms and the CoEd application were stored on a secure server at the Inria research center and anonymized using participants’ identification numbers. Only researchers working on the project are authorized to consult the collected data.

### Statistical Analysis

#### Power

We did not find previous studies assessing the impact of a digital device on IEP teams’ relationships and communication in order to perform a power analysis. However, some behavioral interventions with the same target were published and reported moderate effect sizes. Thus, we based our power analysis on an effect size of *d*=0.600.

#### Planned Statistical Analyses

We plan to conduct pre-post mean comparison analysis on primary (RQ1) and secondary outcomes (RQ2 and RQ3) to assess within and between-team effects of the intervention. We will conduct within-team analyses using 1-way ANCOVA to compare pre and postintervention differences separately for each team’s experimental and control groups. This approach helps identify specific changes within teams and assesses differential effects between groups. Additionally, a between-team analysis will treat all participants as a single population, using repeated-measures ANCOVAs or linear regression analyses to examine the overall intervention effect across teams. This global analysis disregards team distinctions to assess the intervention’s overall impact. In addition, using ANCOVA will allow us to control for potential bias coming from the variability in technological skills (Computer Usage Questionnaire; see Table 1) as well as any variable that may compromise the homogeneity across groups. Missing data will result in the exclusion of related observations, and dropouts will be monitored to explore the reasons.

By combining these methods, we aim to provide a comprehensive evaluation of the psychological intervention’s effectiveness, considering both within-team variation and overall effects.

To assess the user experience (RQ4), only the participants of the CoEd intervention condition answered the user experience questionnaire. These data will be analyzed through descriptive statistics and compared with questionnaire-related benchmarks.

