## Results

The study was funded in 2021 with public funds from Conseil Régional d’Aquitaine and the Fondation International pour la Recherche Appliquée au Handicap (FIRAH), Klesia, and Comité National Coordination Action Handicap (CCAH).

Figure 3 shows the flowchart of the recruitment process. We initially recruited 37 eligible teams who were allocated to either the experimental or control group, which resulted in a sample size of 157 participants (2-7 people per team). At baseline, 31 individuals did not complete the questionnaires, leading to the exclusion of 11 teams due to incomplete data. In September 2023, the recruitment ended with 13 teams participating in the experimental condition (n=82) and 11 teams in the control condition (n=45). The experimental group is larger than the control group due to the nature of our action-research approach. Participants and partners expressed a strong preference for being included in the intervention to benefit from the CoEd app, viewing control group assignment negatively. To address this while maintaining rigorous assessment, we included more participants in the experimental group, ensuring sufficient data for analysis and respecting the ethical considerations of action research.

At the end of data collection (June 2024), a total of 59 individuals had dropped out: They stopped responding to the questionnaires and did not reply to our follow-up attempts. Consequently, there were 89 remaining participants at the 3-month follow-up and 67 participants at the 6-month follow-up. Data cleaning and analysis began in March 2025, and results are expected by June 2025. We anticipate that the findings may be ready for publication by the end of 2025, although this timeline remains provisional.

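### The planned within-team pre-post ANCOVA cannot assess a differential effect between groups: no team contains both conditions, and separate pre-post tests do not compare change between arms

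*Protocol article*

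**What the plan says.** Under Planned Statistical Analyses, the protocol article states: "We will conduct within-team analyses using 1-way ANCOVA to compare pre and postintervention differences separately for each" team's experimental and control groups. It then gives the purpose: "This approach helps identify specific changes within teams and assesses differential effects between groups". A second, pooled analysis (repeated-measures ANCOVA or linear regression on everyone, setting team membership aside) is to give the overall intervention effect. The section closes by saying that the two approaches will be combined to judge effectiveness.

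The Results section describes allocation: "We initially recruited 37 eligible teams who were allocated to either the experimental or control group". It gives the size at recruitment as "a sample size of 157 participants (2-7 people per team" and the position when recruitment ended as "13 teams participating in the experimental condition (n=82) and 11 teams in the control condition (n=45". It reports 89 participants remaining at 3 months and 67 at 6 months. The Power section gives d=0.600 and no alpha, power or pre-post correlation.

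**The concern.** The analysis is specified and given a purpose, and the two do not fit. A comparison of conditions inside a team needs members in both conditions, and the allocation rules that out. What remains is a set of separate pre-post tests, by team or by arm. Each estimates a change. None estimates the difference between two changes, which is what a differential effect is.

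Follow-up ran from September 2023 to June 2024, a school year, so change common to both arms is plausible. The CoEd arm is the larger one, so the same true change is more likely to reach significance there than among controls. Reading that pattern as a differential effect would favour the intervention.

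**Working it through.** **1. Does the comparison exist?** The planned sentence needs experimental and control members in the same team. The Results section places each team wholly in one condition. Condition therefore varies only between teams and cannot be a within-team factor.

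**2. Per-team reading.** Inputs: team size n from 2 to 7 (Results) and d=0.600 (Power). Assumed: two-sided alpha 0.05 and pre-post correlation r=0.5, range 0.3 to 0.7.

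- Residual degrees of freedom for change scores with an intercept and one covariate are n − 2: 0 at n=2 (not estimable), 1 at n=3, 5 at n=7.
- Standardized change: dz = d / √(2(1 − r)) = 0.6 / √(2 × 0.5) = 0.6.
- Power of a paired t test without a covariate (n − 1 df, noncentrality dz√n):

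| n | r=0.3 | r=0.5 | r=0.7 |
|---|---|---|---|
| 2 | 6% | 7% | 8% |
| 3 | 9% | 10% | 13% |
| 4 | 11% | 14% | 20% |
| 5 | 14% | 18% | 27% |
| 6 | 17% | 22% | 34% |
| 7 | 21% | 27% | 41% |

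Mean team size was 157/37 = 4.2 at recruitment. After dropout it is at most 89/24 = 3.7 at 3 months and 67/24 = 2.8 at 6 months if all 24 teams remain. Some primary scales go to one role only (Table 1), so fewer members of a team contribute to those.

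**3. Per-arm reading.** Suppose both arms have the same true change, dz, in SDs of the change score. With p1 and p2 the powers of the CoEd and control pre-post tests, the chance of CoEd significant and control not is p1 × (1 − p2). Participants are treated as independent. The documents give no value for a common change, so a range is shown. The 3-month row splits the 89 in the baseline ratio, an assumption: 89 × 82/127 ≈ 57 and 89 × 45/127 ≈ 32.

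| CoEd vs control | dz=0 | 0.1 | 0.2 | 0.3 | 0.4 | 0.5 |
|---|---|---|---|---|---|---|
| 82 vs 45 | 5% | 13% | 32% | 38% | 24% | 9% |
| 57 vs 32 | 5% | 11% | 26% | 38% | 34% | 21% |

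Example, 82 vs 45 at dz=0.3: 0.766 × (1 − 0.503) = 0.38. In every cell the true differential effect is zero.

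**The case against.** The strongest reply is that the pooled analysis carries the overall intervention effect and can contain a direct between-group contrast, so the within-team step is only supportive. That stands in part. A reader might infer that the plan has no route to a group comparison at all, or that the investigators will declare an effect when only the CoEd arm is significant. The documents support neither: the pooled route exists, and no decision rule of that kind is stated. But the text attaches the differential claim to the within-team step and combines both steps to judge effectiveness. The pooled step also ignores the unit that was allocated.

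Three further limits stand.

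- The sentence is ambiguous, and its possible defects belong to different readings. Zero degrees of freedom in a two-person team follows if change scores are analysed. Treating repeated measures as independent follows only if pre and post enter as separate rows. The wording on pre-post differences fits change scores better, so the second defect is conditional.
- The 2-to-7 range describes the 37 recruited teams. If 7 is still the maximum, 13 CoEd teams could hold 13 × 7 = 91, and 91 − 82 = 9. Each two-member team uses up 5 of those 9, so at most one CoEd team had two members at allocation. The inestimable case is mainly a control-team or post-dropout problem. The named covariate, the Computer Usage Questionnaire, is listed for the intervention group only, so in control teams it would have to be some other variable.
- It is tempting to count 24 teams × 6 primary instruments = 144 tests and expect 144 × 0.05 ≈ 7 false positives. That is not supported: two of the six instruments are for a single role, and some per-team tests could not be run.

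**Conclusion.** Wrong as written. The within-team ANCOVA refers to groups that no team contains, and neither reading delivers the differential effect claimed for it. This does not depend on any assumed number.

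The size does. Per team, power is about 7% to 27% at d=0.600, given r=0.5 and two-sided 0.05. Per arm, the chance of the misleading one-arm-only pattern under equal change is 5% to 38% across common changes of 0 to 0.5 SD, at either set of sample sizes. The 38% should not be taken as the error rate of the plan: it is the highest of the values examined, and it rests on an assumed common change and on arm totals that role-specific scales would not reach.

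**What to change.** In Planned Statistical Analyses:

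- Delete the claim that the within-team analysis assesses differential effects, and drop per-team and per-arm p values.
- Take the differential effect from one direct contrast on all participants: group by time, or the between-group difference at follow-up adjusted for baseline.
- Replace the pooled analysis that sets teams aside with a model that includes team as a random effect. No such model is in the current text, so it has to be written in.
- Show team-specific change descriptively, with intervals.
- Date the change and label it as made after analysis began, which the Results section puts in March 2025.

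No new data are needed. The cost is analysis work, the loss of tests that carry little information, and probably a wider interval for the intervention effect once team is modelled.

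### Teams were allocated, but the planned between-group analysis ignores team, so outcomes with several respondents per team get standard errors that are too small

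*Protocol article*

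**What the plan says.** The Results section of the protocol article makes the team the unit of allocation: "We initially recruited 37 eligible teams who were allocated to either the experimental or control group". After baseline losses, 13 teams (82 people) remained in the CoEd condition and 11 teams (45 people) in control. Teams had 2 to 7 members at recruitment. By the follow-ups, 89 and then 67 participants remained.

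Planned Statistical Analyses describes two strands. The first is a within-team one-way ANCOVA meant to "compare pre and postintervention differences separately for each team’s experimental and control groups". The second carries the overall effect: "a between-team analysis will treat all participants as a single population, using repeated-measures ANCOVAs or linear regression analyses". Of this strand the article adds: "This global analysis disregards team distinctions". Missing data lead to exclusion of the observation. No random team effect, cluster-robust error, ICC or design effect appears.

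The Power section reads "Thus, we based our power analysis on an effect size of" d=0.600, with no sample size, alpha, power or allowance for clustering beside it.

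Table 1 shows that respondents differ by outcome. Parents, teachers and professionals all answer the Helping Alliance Questionnaire, the Basic Psychological Need scale, the Goal Attainment Scale and the WHOQOL-BREF. The Parent-Teacher Relationship Scale goes to parents and teachers. The two attitude scales each go to one role, and several child outcomes are answered by the pupil alone.

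**The concern.** People in the same team share a pupil, a set of working relationships and, in the CoEd arm, one shared file. On the relationship scales they rate their dealings with one another. Their changes over the study may therefore be correlated. When the team is the unit that receives the condition, the information about the condition comes from differences between teams: 24 of them, or about 22 degrees of freedom. A model that counts 127 independent people uses about 125.

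Repeated-measures ANCOVA accounts for repeated measurements within a person, not for people within a team. The within-team strand does not fill the gap. Each team sits in one condition only, so that strand contains no between-arm contrast with a team-level error term.

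At stake are the P values and confidence intervals for the between-group effect on outcomes with several respondents per team, three of which are primary.

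**Working it through.** **No figure to reproduce.** The article states d=0.600 but no N, alpha or power, so there is no calculation of its own to repeat.

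**Inputs from the article.** 82 people in 13 teams (mean 82/13 = 6.31); 45 in 11 teams (mean 45/11 = 4.09); 89 and 67 people at the follow-ups. The flow counts do not quite add up (157−31 = 126 against 127; 37−11 = 26 teams against 24; 127−59 = 68 against 67), but this does not affect the conclusion.

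**Assumptions.** Two-sided alpha 0.05. ICC of the analysed (change or baseline-adjusted) score 0.05, 0.10, 0.20 or 0.30. Near-equal team sizes within each arm. Follow-up numbers split in the baseline arm ratio (57/32 and 43/24).

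**Formulas.**
- Arm design effect: DE = 1 + (Σm²/Σm − 1) × ICC.
- Variance ratio: R = (DE₁/n₁ + DE₂/n₂) / (1/n₁ + 1/n₂).
- Actual type I error of the pooled test: 2 × [1 − Φ(1.96/√R)].

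**Worked case: baseline sizes, ICC 0.10.**
- CoEd arm: four teams of 7 and nine of 6, so Σm² = 520, 520/82 = 6.34 and DE₁ = 1 + 5.34 × 0.10 = 1.534.
- Control arm: one team of 5 and ten of 4, so Σm² = 185, 185/45 = 4.11 and DE₂ = 1 + 3.11 × 0.10 = 1.311.
- R = (1.534/82 + 1.311/45) / (1/82 + 1/45) = 0.04784/0.03442 = 1.39.
- The standard error is too small by a factor of √1.39 = 1.18. Type I error = 2 × [1 − Φ(1.96/1.18)] = 9.6%.

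**Actual type I error of a nominal 5% pooled test (multiple of nominal in brackets).**

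| Setting | ICC 0.05 | 0.10 | 0.20 | 0.30 |
|---|---|---|---|---|
| Baseline, 127 in 24 teams | 7.3% (1.5) | 9.6% (1.9) | 14.2% (2.8) | 18.3% (3.7) |
| 89 people, whole teams lost (17 teams left, illustrative) | 7.3% (1.5) | 9.6% (1.9) | 14.1% (2.8) | 18.2% (3.6) |
| 89 people over all 24 teams | 6.4% (1.3) | 7.9% (1.6) | 10.9% (2.2) | 13.8% (2.8) |
| 67 people over all 24 teams | 6.0% (1.2) | 6.9% (1.4) | 8.9% (1.8) | 10.9% (2.2) |
| Two respondents per team | 5.6% (1.1) | 6.2% (1.2) | 7.4% (1.5) | 8.6% (1.7) |
| One respondent per team | 5.0% | 5.0% | 5.0% | 5.0% |

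Simulation (20,000 trials per cell) agrees with the formula. For the whole-team-loss row, the pooled t test rejected in 7.4, 9.6, 14.5 and 18.5% of trials. A t test on team means held 4.3 to 5.1% across the settings simulated. Uneven team sizes raise the rate somewhat: with illustrative control sizes of 7, 7, 6, 5, 4, 4, 3, 3, 2, 2, 2, the baseline row becomes 7.6, 10.3, 15.3 and 19.9%.

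**What 24 teams can detect.** Noncentral t with 22 df and noncentrality d/√(DE₁/n₁ + DE₂/n₂), for outcomes answered by all adults:

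| | ICC 0.05 | 0.10 | 0.20 | 0.30 |
|---|---|---|---|---|
| Power at d=0.6, 127 people | 81% | 75% | 64% | 56% |
| d detectable with 80% power, 127 people | 0.595 | 0.641 | 0.726 | 0.801 |
| Power at d=0.6, 89 people over 24 teams | 69% | 64% | 57% | 50% |
| d detectable with 80% power, 89 people | 0.687 | 0.723 | 0.792 | 0.855 |

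**The case against.** Several objections have force, and they limit the point.

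- **Scope.** A reader might infer that every primary and secondary test is affected. Table 1 does not support that. There is one pupil per team, so child-reported outcomes give one observation per team. Parent-only and teacher-only scales have no inflation where one person per team answers, and little where two do.
- **Size.** A reader might infer a false-positive rate of 2 to 4 times nominal as a general figure. At baseline team sizes, a doubling needs an ICC of about 0.11 and a fourfold rate about 0.34. With 89 people spread over all teams these become 0.17 and 0.54, and with 67 people 0.25 and 0.81. The article does not say how dropout fell across teams.
- **Which correlation.** The relevant ICC is that of change or baseline-adjusted scores. Stable differences between teams largely cancel in change, and the Goal Attainment goals were set independently. Nothing in the article shows that 0.20 or 0.30 is realistic.
- **Status of the analysis.** A reader might call the pooled analysis the main one. The article does not. It introduces it as an addition to the within-team strand and says the methods are combined. It is, however, the only strand given the job of estimating the overall effect.
- **Power.** A reader might conclude that a stated power is refuted. None is stated, so the power figures above are orientation only.

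What remains is the stated rule to ignore team. This is not a detail left to an unseen analysis plan: the article fixes it in words, and no other section corrects it.

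**Conclusion.** The point holds for outcomes answered by several members of a team. It applies with most force to the Helping Alliance, Basic Psychological Need, Goal Attainment and WHOQOL-BREF scores, and less to scales with about two respondents per team. With any positive within-team correlation in the analysed score, the pooled analysis understates the standard error. For ICCs of 0.05 to 0.30 on all-adult outcomes, the standard error is too small by a factor of 1.09 to 1.47 at baseline team sizes. The type I multiples run from 1.2 (67 people spread over all teams, lowest ICC) to 3.7 (baseline team sizes, highest ICC).

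These sizes rest on an assumed ICC, an assumed 5% level, near-equal team sizes within arm and an assumed dropout pattern. The direction rests only on the correlation being positive. The documents do not support extending the point to one-respondent scales or treating any one multiple as established.

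**What to change.** In Planned Statistical Analyses, replace the pooled analysis according to how many people per team answer the outcome:

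- **Several respondents per team:** a linear mixed model with group, time, group-by-time and respondent role as fixed effects, and random effects for team (with team-by-time where estimable) and participant. Use Kenward-Roger or Satterthwaite degrees of freedom. If this is unstable with 24 teams, use a team-mean analysis or a regression with CR2 small-sample cluster-robust errors. The Helping Alliance Questionnaire has a 13-item parent form and an 11-item professional form, so its raw totals need a common scale before roles are combined.
- **One respondent per team:** ordinary baseline-adjusted ANCOVA is enough, since team and participant variance cannot be separated.

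Report the ICC for each multi-respondent outcome. State beside d=0.600 the effect detectable with 24 teams over a range of ICCs.

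Collection ended in June 2024 and data cleaning and analysis began in March 2025, so disclose this as a change made after data collection. It needs no new data, only the team identifiers. The cost is wider confidence intervals and a less favourable detectable effect. It corrects the standard errors; it does not remove bias from non-random allocation.
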